## Abstract

**Background:**

Type 2 Diabetes Mellitus (T2DM) is common, affecting nearly 400 million people worldwide. Achieving good health for people with T2DM requires active self-management; however, uptake of self-management education is poor, and there is an urgent need to find better, more acceptable, cost-effective methods of providing self-management support. Web-based self-management support has many potential benefits for patients and health services. The aim of this trial is to determine the effectiveness and cost-effectiveness of a web-based self-management support programme for people with T2DM.

**Methods:**

This will be a multi-centre individually randomised controlled trial in primary care, recruiting adults with T2DM who are registered with participating general practices in England. Participants will be randomised to receive either an evidence-based, theoretically informed, web-based self-management programme for people with T2DM which addresses medical, emotional, and role management, called Healthy Living for People with type 2 Diabetes (HeLP-Diabetes) or a simple information website. The joint primary outcomes are glycated haemoglobin (HbA1c) and diabetes-related distress, measured by the Problem Areas In Diabetes (PAID) questionnaire. Secondary outcomes include cardiovascular risk factors, depression and anxiety, and self-efficacy for self-management of diabetes. Health economic data include health service use, costs due to the intervention, and EQ-5D for calculation of Quality Adjusted Life Years (QALYS). Data will be collected at baseline, 3 months and 12 months, with the primary endpoint at 12 months. Practice nurses, blinded to patient allocation, collect clinical data; patients complete online questionnaires for patient reported measures. A sample size of 350 recruited participants allows for attrition of up to 15 % and will provide 90 % power of detecting at a 5 % significance level a true average difference in the PAID score of 4.0 and 0.25 % change in HbA1c (both small effect sizes). The analysis will follow a pre-specified analysis plan, based on comparing the groups as randomised (intention-to-treat).

**Discussion:**

The findings of this trial are likely to be of interest to policy makers, clinicians, and commissioners, all of whom are actively seeking additional forms of self-management support for people with T2DM.

**Trial registration:**

The Trial Registration number is ISRCTN 02123133; date of registration 14.2.13.

## Background

Type 2 diabetes (T2DM) is one of the commonest long term conditions affecting nearly 400 million people worldwide [1] and over 3 million in the UK [2]. T2DM can cause severe complications including cardiovascular disease, blindness, renal failure and neuropathy, and can reduce life expectancy by 8 – 10 years [3]. In the UK, approximately 12 % of deaths of people between the ages of 20 – 79 years are attributable to diabetes and about 10 % of the NHS budget (£9 billion per annum) is spent on diabetes [4]. Many of these costs are due to preventable complications. The key to good clinical outcomes in people with diabetes is self-management which can reduce both the incidence and impact of complications. Structured education is known to promote self-management and reduce the incidence of diabetes complications [5–7]. In 2008, the National Institute for Health and Care Excellence (NICE) advised that all patients with diabetes should be offered structured education at the time of diagnosis with annual reinforcement [3]. NICE advised that such structured education or self-management programmes (SMP) should improve outcomes through addressing health beliefs, optimising metabolic control, addressing cardiovascular risk factors, facilitating behaviour change, improving quality of life and reducing depression as well as enhancing the relationship between the patient and their healthcare professionals [3].

Examples of existing self-management programmes for people with type 2 diabetes in the UK include DESMOND [7], X-PERT [8] and Co-Creating Health [9]. Although these programmes have shown initial benefits, there are concerns that benefits may not be sustained in the long term [10]. There are additional concerns that group-based programmes such as these may not suit all patients who need self-management training. People who work, have caring responsibilities at home, have mobility problems, or who find group interactions difficult may all have difficulty attending. Thus there is an urgent need to find cost-effective and acceptable methods of delivering sustainable self-management education for people with type 2 diabetes in the UK. One possibility is the use of web-based or computer-based self-management programmes. These have many potential advantages, including convenience, accessibility and anonymity. For people with home access to the internet (84 % of UK households in 2014) [11], such programmes can be accessed at any time of day or night so can be fitted in around responsibilities at home or work. Information can be presented accessibly using simple graphics or audio-visual techniques and can be easily updated as new research becomes available. Programmes can be highly interactive, responding to data entered by individual users to provide a tailored, personalised experience. They can offer structured behaviour change support including self-assessment, goal-setting, monitoring and feedback. Users can gain emotional support from reading about others’ experiences with similar problems (personal stories), participating in online forums, or using online support tools such as computerised cognitive behavioural therapy or mindfulness training. Unlike face-to-face interventions, computerised programmes can be permanently available and provide both on-going support as well as meeting changing needs as the disease progresses. The marginal costs per additional user are low, so such interventions have the potential to be highly cost-effective. A recent Cochrane systematic review of such programmes suggested they can improve some health outcomes including glycaemic control, weight and lipids, but there were insufficient data to draw any conclusions about their impact on emotional well-being, quality of life or cost-effectiveness. None of these programmes addressed all the areas specified by NICE for self-management education, and none were developed in the UK [12].

We have developed a web-based self-management programme for people with type 2 diabetes known as HeLP-Diabetes, or Healthy Living for People with type 2 diabetes. HeLP-Diabetes was developed as part of a National Institute for Health Research (NIHR) Programme Grant for Applied Research. The content and development of HeLP-Diabetes was based on five main principles: first, we adopted the Corbin and Strauss model of the work required for self-management of a long-term condition, which includes medical management (e.g. adopting healthy behaviours, working with health professionals, managing medicines), emotional management (e.g. managing the strong negative emotions resulting from being diagnosed with a long term condition including anger, guilt, shame and despair), and role management (e.g. managing the disruption of one’s biographical narrative) [13]. This model gave us an overarching framework of patients’ requirements. Secondly we undertook extensive qualitative work with our target users, defined as patients with type 2 diabetes and health professionals who care for these patients, to identify user needs and wants from such a programme. Effective self-management requires a partnership between patients and health professionals so it was important to ensure that the programme was acceptable to both groups of users. User input continued throughout the development process with user panels providing iterative comments on materials as they were developed and refined (participatory design), ensuring that the final programme was highly acceptable to both patients and health professionals. Thirdly, we reviewed the behaviour change literature to identify behaviour change techniques that were most likely to be effective in helping patients achieve sustainable behaviour change. Fourthly, we applied the principles of Normalization Process Theory (NPT) to maximise the likelihood of the programme being easily implemented and integrated into routine NHS care [14]. Finally, we ensured that all information provided in the programme was evidence-based and compatible with current NICE guidelines.

## Methods/design

### Aims and objectives

The aims of the trial are to:Determine the effect of HeLP-Diabetes on clinical outcomes and health related quality of life in people with T2DMDetermine the incremental cost-effectiveness of the intervention from the perspectives of health and personal social services and wider public sector resources.

Hypothesis: that use of the intervention will improve diabetes-related quality of life and health status.

### Design

Multi-centre, two-arm individually randomised controlled trial in primary care.

### Ethics and trial registration

This trial received ethical approval from Camden and Islington Research Ethics Committee reference 12/LO/1571. The Trial Registration number is ISRCTN 02123133.

### Setting

General practices in England.

### Participants

Inclusion criteria:Adults aged 18 or over, with type 2 diabetes.

Exclusion criteria:Unable to provide informed consent e.g. due to psychosis, dementia or severe learning difficultiesTerminally ill with less than 12 months life expectancyUnable to use a computer due to severe mental or physical impairmentInsufficient mastery of spoken or written English to use the intervention

Participants do not have to have home internet access or prior experience of using the internet to participate. Participants with previous or current experience of self-management education are eligible to participate.

### Recruitment

Approximately 20 practices will be recruited through 5 Primary Care Research Networks (PCRN) in England (South West Central, East of England, South East, Greater London) and the North Central London Research Consortium (NoCLOR). Practices will be assessed for their feasibility (e.g. large enough diabetes register to be able to invite a minimum of 300 eligible participants; staff are trained in Good Clinical Practice (GCP); 2 members of staff available to carry out the study so that 1 can support the participant in use of the intervention and the other can remain blinded for data collection) prior to agreement to act as a participating site. Once a practice has agreed to participate and completed site set-up procedures they will commence patient recruitment.

Patient recruitment will follow standard opt-in procedures. Each practice will have a register of patients with type 2 diabetes as they need this for the Quality and Outcomes Framework. A nurse or other qualified health professional will review the electronic medical record of each of the patients on this register with a view to screening out ineligible patients. All remaining potentially eligible patients will be sent a letter from their GP, inviting them to participate in the study. A participant information sheet, consent form, expression of interest and stamped addressed envelope will be included. Patients who are interested in participating will be asked to return the expression of interest form to the trial manager.

In addition posters advertising the study will be put up in each practice so that patients can ask a clinician directly for more information about taking part.

On receipt of the expression of interest form the nurse will contact the patient and offer them an appointment at the practice. At this appointment, patients will be given an opportunity to discuss the pros and cons of participation, and those that agree to participate will be asked to sign the written consent form. After signing the consent form, participants will be asked to complete baseline data collection procedures prior to randomisation. Randomisation marks the point of entry into the trial.

### Randomisation

Randomisation will be performed only after all baseline data collection has been completed. Randomisation will be at the level of the individual participant. It will be stratified by recruitment centre and will be performed centrally using a web-based randomisation system provided by an independent contractor (Sealed Envelope http://www.sealedenvelope.com/). This system will send an email to the trial manager when a patient has been randomised detailing which arm the patient has been allocated to. This will then be forwarded to the nurse who will be introducing the control and intervention websites to the patients in visit 2.

### Intervention

The intervention consists of facilitated and supported access to HeLP-Diabetes. There are three components to the supported access: first an introductory session, secondly supportive follow-up phone calls, and thirdly, on-going discussion of patient’s self-management goals in routine appointments for diabetes-related matters.

In the introductory session practice nurses will give the patient a booklet containing the uniform resource locator (URL) for the programme, the participant’s log in details, and information about the content of the website and how best to use it. Nurses will show the patient how to access the website, and introduce them to the main content areas. The nurse will discuss with the patient what the patient’s most pressing needs are and use this to guide the patient toward certain sections (for example, improving diet, being more physically active, or managing emotions). Follow-up phone calls will be offered to support the patient in use of the programme. Nurses and doctors in participating practices will be encouraged to refer to the programme in consultations with participating patients and to integrate information from the programme into management plans.

HeLP-Diabetes is a web-based programme with multiple components. There are information sections  including how diabetes is treated, possible complications of diabetes, possible impacts of diabetes on relationships at home and at work, dealing with unusual situations like parties, holidays, travelling or shift work, and what lifestyle modifications will improve health. There are sections addressing skills and behaviour change, including behaviour change modules on eating healthily, losing weight, being more physically active, smoking cessation, moderating alcohol consumption, managing medicines, glycaemic control and blood pressure control. These all include motivating information on the benefits of behaviour change, self-assessment quizzes for patients to assess whether and how much they need to change, and opportunities for goal-setting and self-monitoring. The third strand of components focuses on emotional well-being and contains self-help tools based on cognitive behavioural therapy and mindfulness. There are multiple personal stories (used with license from healthtalk.org), and a moderated forum for users to interact with each other.

### Comparator

From an NHS perspective the important research question is whether the proposed intervention can improve health outcomes when compared to current practice. However, to improve acceptability to participants and help maintain blinding, all participants will have access to a website. Participants in the control arm will have access to a simple information website, based on the information available on the Diabetes UK and NHS Choices websites. These participants will also be given a booklet with the URL and user log in details, and will also have the introductory session with the nurse explaining how to use the website and offer of follow-up phone calls. However, as the website will have no behaviour change components, no emotional support and only simple information, it is unlikely that there will be many opportunities to refer to it in diabetes-related appointments.

### Outcomes and outcome measures

#### Primary outcomes

The outcomes reflect our aims of improving clinical outcomes and health related quality of life. We have selected two joint primary outcomes: glycated haemoglobin (HbA1c) and diabetes-related distress measured by the Problem Areas in Diabetes (PAID) scale [15]. PAID has 20 items focusing on areas that cause difficulty for people living with diabetes, including social situations, food, friends and family, diabetes treatment, relationships with health care professionals and social support. It has been the subject of a number of reviews comparing available quality of life measures for diabetes. Eigenmann assessed available measures against criteria of: reliability; content, face, construct, criterion and convergent validity; responsiveness to change; interpretability; response burden; acceptability; and availability and concluded that PAID was one of three measures that met all criteria [16]. It is sensitive to change and has been widely used to evaluate self-management programmes for people with T2DM including the influential DESMOND trial [7].

#### Secondary outcomes

Secondary outcomes have been selected to reflect the proposed pathway of action of our intervention and allow health economic analysis and can be categorised as clinical, patient-reported, or economic.

#### Clinical outcomes include:

Systolic and diastolic blood pressureBody mass index;Total cholesterol and HDL (not fasting)Completion of “9 essential processes” [3] (= weight, BP, smoking status, measurement of serum creatinine, cholesterol and HbA1c, urinary albumin and assessment of eyes and feet).

Patient-reported outcomes:Depression and anxiety measured using the Hospital Anxiety and Depression Scale (HADS) [17]Diabetes-related self-efficacy measured using the Diabetes Management Self-Efficacy Scale (DMSES) [18]Satisfaction with treatment measured using the Diabetes Satisfaction with Treatment Questionnaire status and change version (DTSQs & DTSQc) [19].

Economic outcomes:Cost of developing the interventionCost of supported accessCosts of training NHS staff both in using the intervention and training patients to use the interventionCosts of maintaining and updating the interventionHealth care and social service utilisation during the study periodEQ-5D to calculate QALYs [20]Clinical parameters required for modelling long term cost-effectiveness of the intervention (detailed below).

In addition we will use automated software to record each participant’s use of the intervention (number and frequency of log-ins, pages visited).

### Data collection

Data to describe our patient population will be collected at baseline and will include demographic and clinical data.

Demographic data will include: age, gender, highest educational attainment, ethnicity, current employment status, presence or absence of home internet access, level of expertise in computer use, and current or previous participation in diabetes self-management education.

Baseline clinical data to be obtained from the medical record will include:date of diagnosis of diabetesHbA1c, blood pressure, total cholesterol, HDL cholesterol and smoking status at time of diagnosispresence or absence and date of diagnosis of complications of diabetes including ischaemic heart disease, myocardial infarction, congestive cardiac failure, atrial fibrillation, peripheral vascular disease, amputation, cerebro-vascular disease, retinopathy, renal failure and neuropathya list of current medicationsAdditional clinical data on height (cm) weight (kg), systolic and diastolic blood pressure, current smoking status, and current levels of HbA1c, total cholesterol and HDL cholesterol will also be obtained during the baseline visit

Baseline patient reported outcomes include:PAIDHADSDTSQEQ-5DDMSES

Baseline health economic data includes:Clinical data as aboveHealth service utilisation in the 12 months prior to baseline visit.

Follow up data will be collected at 3 and 12 months with 12 months as the primary outcome point. At follow-up data will be collected on the clinical and patient reported outcomes listed above, along with attendance at alternative self-management education. Demographic data will only be collected at baseline.

Data on use of health service utilisation will be collected for the past 12 months at baseline, the past 3 months at 3 month follow-up and the past 9 months at 12 month follow-up. Data on completion of the “9 essential processes” will be collected from the GP record for the 12 months prior to randomisation and the 12 months after randomisation at the 12 month follow-up point to avoid triggering behaviour change amongst the study nurses.

Standard operating procedures (SOPs) will cover every aspect of data collection and nurses will be trained in these procedures. Adherence to SOPs will be monitored. Participants will complete self-reported questionnaires (demographics, PAID, HADS, DMSES, DTSQ, EQ-5D and community and social service use) online, prior to the nurse recording clinical outcomes and taking blood for HbA1c and lipids. Clinical data will be entered directly into the online database by the nurse. Data on utilisation of primary and secondary health care services will be extracted from the clinical record by the nurse.

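### The nine-process outcome is read from the GP record over windows in which trial visits perform five of the nine processes before randomisation and at least four after it

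*Protocol article*

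**What the plan says.** The list of clinical secondary outcomes in the protocol article defines the nine processes as "weight, BP, smoking status, measurement of serum creatinine, cholesterol and HbA1c, urinary albumin and assessment of eyes and feet". The Data collection section fixes the source and the periods: the information is "collected from the GP record for the 12 months prior to randomisation and the 12 months after randomisation". Extraction waits until the 12-month follow-up, "to avoid triggering behaviour change amongst the study nurses".

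The same section lists what is obtained at the baseline visit, including "height (cm) weight (kg), systolic and diastolic blood pressure, current smoking status, and current levels of HbA1c, total cholesterol and HDL cholesterol". The Randomisation section places that visit before allocation: "Randomisation will be performed only after all baseline data collection has been completed". On later visits, Data collection says "Follow up data will be collected at 3 and 12 months with 12 months as the primary outcome point" and "At follow-up data will be collected on the clinical and patient reported outcomes listed above". Participants complete their questionnaires "prior to the nurse recording clinical outcomes and taking blood for HbA1c and lipids".

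Data collection sends the clinical data straight to the trial's online database. It does not say whether the same values are also written to the GP record. The article states no rule on whether entries arising from a trial visit count towards the nine.

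**The concern.** The Secondary outcomes section says these outcomes were chosen to reflect how the intervention is expected to work, so this one should show whether the programme leads people to obtain recommended care. The authors saw that the trial could disturb it, since they delay extraction so as not to prompt the nurses. Delay deals with prompting only. It cannot remove measurements that the trial itself schedules inside both windows.

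Wherever trial results reach the GP record, the affected items are complete for every attender in either arm, whatever routine care was given. Completion rates would then overstate routine care. A real difference between arms could be diluted, and a null result could partly reflect the visit schedule. If practices differ in what they transcribe, the count would also partly reflect local recording habits.

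**Working it through.** **Step 1. Count the overlap.** The article's figure of nine is reproduced by counting its list: weight, blood pressure, smoking status, creatinine, cholesterol, HbA1c, urinary albumin, eyes, feet.

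- *Before randomisation.* The baseline visit covers weight, blood pressure, smoking status, HbA1c and cholesterol. It precedes randomisation, so it lies in the first window: 5/9 = 56%.
- *After randomisation.* Follow-up visits collect the listed clinical outcomes. These include blood pressure, body mass index (which needs weight) and total cholesterol, and blood is taken for HbA1c and lipids: 4/9 = 44%. Smoking status is not among the listed outcomes, so its re-recording is uncertain; with it, 5/9 = 56%. The 3-month visit lies well inside the window and is enough by itself, so it does not matter that the 12-month visit falls at the edge.
- *Never performed by the trial, as described.* Creatinine, urinary albumin, eyes and feet, plus smoking status in the second window if it is not re-recorded.

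**Step 2. Share of a 0-9 count met by trial attendance in the second window.** Let k be the number of overlapping items, a the proportion attending and r the proportion of trial measurements that reach the GP record.

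Share = k × a × r / 9

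The article gives no r, so it is varied from 0 to 1. For a, I use full attendance and 85%; the latter takes the article's allowance of up to 15% attrition as a stand-in for missed visits.

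| k | a | r = 0 | r = 0.5 | r = 1 |
|---|---|---|---|---|
| 4 | 1.00 | 0% | 22% | 44% |
| 4 | 0.85 | 0% | 19% | 38% |
| 5 | 1.00 | 0% | 28% | 56% |
| 5 | 0.85 | 0% | 24% | 47% |

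For example, 4 × 0.85 × 1 / 9 = 0.378.

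**Step 3. Loss of signal at the upper end (a = r = 1).** Suppose the programme raises each routine process by the same amount d.

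- *Raw mean difference.* It falls from 9d to 5d (k = 4) or 4d (k = 5). The loss is 1 − 5/9 = 44% or 1 − 4/9 = 56%.
- *Standardised difference.* Items fixed at complete in both arms lose variance as well as difference. For m free, independent items with common SD s, the difference is m·d, the SD is s·√m, and the ratio is √m·d/s. The loss against nine items is 1 − √(5/9) = 25% or 1 − √(4/9) = 33%. If the items were perfectly correlated, the ratio would be d/s for any m and the loss would be zero.

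**Step 4. Dependence on scoring.** The article speaks only of completion. The arithmetic in steps 2 and 3 applies to a 0-9 count. If the score is whether all nine were completed, the four or five items that the trial does not perform decide it. The arms would then in effect be compared on those items, with overall completion still inflated.

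**The case against.** The strongest objection is that the mechanism depends on something the article does not state. Clinical data go to the trial's online database, while the nine processes are read from the GP record; if the two never meet, there is no problem. That stands as a limit on size. It does not remove the point. The Abstract has practice nurses collecting clinical data, the Recruitment section requires a second member of practice staff to stay blinded for that purpose, and the section on adherence and loss to follow-up has practice nurses offering the follow-up appointments. Entry into the practice record is therefore plausible, although the section on concealment and blinding speaks of research nurses.

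A second objection is that handling of trial-dated entries is extraction detail, which an article may leave to standard operating procedures or an analysis plan that are not shown. That is fair as regards the missing rule. But the source, the windows and the extraction time are fixed here, and following them as written gives a diluted measure wherever trial results reach the record.

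Third, equal effects on every item are an assumption. If the overlapping processes are already done for nearly everyone in routine care, little signal is lost. The article gives no completion rates, so this cannot be settled.

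Two stronger readings are tempting. A reader might infer that about half of the outcome is fixed by the protocol. The document does not support that: it is the upper end of a range that starts at zero. A reader might also infer that the comparison is biased towards benefit, or that baseline adjustment is invalid. The visit schedule is the same in both arms, so the main effect is dilution. Loss of variation at baseline costs precision and does not bias a randomised comparison. Unequal attendance could show up as a difference in care, but nothing in the article gives reason to expect it.

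**Conclusion.** The overlap is real and follows from the text: five of the nine processes are performed by the trial in the pre-randomisation window and at least four in the post-randomisation window. Late extraction does not separate these from routine care.

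How much this matters rests on three things the article leaves open: whether trial measurements reach the GP record, whether smoking status is re-recorded, and how completion is scored. The loss figures also assume equal effects across items and, for the standardised loss, independence and equal variance.

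This is one secondary outcome. The two primary outcomes do not depend on the GP-record extraction, and the sample size was set on those alone. The point is a worthwhile, inexpensive improvement to the outcome definition; it does not threaten the trial's main conclusions.

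**What to change.** Before extraction begins, specify that the between-arm comparison is made on, or reported separately for, the processes that the trial does not perform: serum creatinine, urinary albumin, eye assessment and foot assessment. Add smoking status if follow-up visits do not record it. Keep the full nine-item count as a descriptive result, and state whether trial-visit measurements are entered in the GP record.

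Counting the nine after removing entries dated on a trial visit should be a sensitivity analysis only. A trial measurement may have replaced a routine one, and strict exclusion would then score delivered care as missing.

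The cost is a line or two in the outcome definition and extraction form. The drawback is a shorter scale that compares less directly with published nine-process figures; the descriptive nine-item count partly makes up for this.
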